## Abstract

Vitamin D insufficiency remains common in adults, and supplementation with cholecalciferol (vitamin D_3_) is widely used to improve circulating 25-hydroxyvitamin D [25(OH)D]. At the same time, circular-economy strategies are increasingly applied to nutraceutical production, including the valorization of fish processing by-products as sources of lipid-soluble bioactives. However, clinical evidence directly comparing fish processing by-product-derived vitamin D_3_ with conventional synthetic vitamin D_3_ at commonly used nutritional doses remains limited. D-FISH is a single-center, randomized, double-blind, parallel-group, non-inferiority trial enrolling adults aged 18–60 years with a baseline plasma of 25(OH)D 20–40 ng/mL. Participants will be randomized (1:1) to receive either fish processing by-product-derived or synthetic vitamin D_3_ at the same nutritional dose (600 IU once daily with the evening meal) for 12 weeks. The primary endpoint is the between-group difference in the change in plasma 25(OH)D from day 0 to day 84, assessed against a pre-specified non-inferiority margin of 5 ng/mL, with analyses conducted in full analysis and per-protocol populations. Secondary endpoints include markers of mineral metabolism (calcium, phosphorus, PTH), fasting lipid profile, anthropometrics, and tolerability/safety outcomes; early 25(OH)D kinetics will be explored at 72 h, day 7, and day 28. The study will inform biochemical non-inferiority and short-term tolerability but is not powered to evaluate clinical outcomes (NCT07127796).

## 1. Introduction

Vitamin D is a fat-soluble vitamin with hormone-like properties that plays a central role in calcium and phosphorus homeostasis, primarily by enhancing intestinal mineral absorption and supporting bone mineralization [1,2]. Two main forms are recognized: vitamin D_2_ (ergocalciferol), mainly derived from plant sources, and vitamin D_3_ (cholecalciferol), which is synthesized in the skin upon exposure to ultraviolet B (UVB) radiation and is also present in animal-derived foods such as fatty fish, liver, and egg yolks [1,2]. In both clinical practice and research, circulating 25-hydroxyvitamin D [25(OH)D] is considered the most appropriate biomarker for assessing vitamin D status [2,3].

Beyond its established skeletal role, vitamin D has been investigated for broader biological effects, including potential contributions to muscle function and immune regulation [2,4]. This wider biological interest has also been translated into large-scale clinical research programs exploring possible links with non-skeletal outcomes, such as cancer, cardiovascular risk, respiratory effects, autoimmune diseases, diabetes, and mortality [4,5]. Evidence regarding lipid-related effects of vitamin D supplementation remains inconsistent, with umbrella evidence suggesting more reproducible (albeit modest) effects on triglycerides (TG), while findings across total, LDL-, and HDL-cholesterol fractions are mixed; therefore, cardiometabolic markers are included here as exploratory correlates rather than efficacy outcomes [6]. However, evidence from randomized controlled trials on extra-skeletal endpoints has often been heterogeneous or largely neutral, with methodological explanations including the enrollment of vitamin D-replete participants, reverse causality, and outcome-specific differences in trial design and baseline risk [4,5]. Accordingly, the clinical interpretation of vitamin D as a pleiotropic modulator remains an active area of debate, particularly regarding which baseline 25(OH)D levels should be considered optimal and for which outcomes [4,7].

At the regulatory level, the European Food Safety Authority (EFSA) has supported authorized health claims for vitamin D, including its contribution to normal absorption and utilization of calcium and phosphorus, maintenance of normal blood calcium concentrations, and maintenance of normal bones and muscle function, as well as normal immune function; EFSA has also substantiated a claim related to reduction in the risk of falling in older adults under defined conditions of use [4,8,9]. Notably, the operational definition of “suboptimal” vitamin D status varies across recommendations, reflecting different public health and clinical perspectives; an additional challenge is the incomplete standardization of 25(OH)D assays, which complicates comparisons across studies and limits data pooling and meta-analyses [4].

Despite these ongoing uncertainties, low 25(OH)D concentrations remain common across Europe and represent a relevant public health issue. In a large, standardized assessment of European populations, the prevalence of circulating 25(OH)D < 50 nmol/L (approximately <20 ng/mL) was estimated at around 40%, with higher rates during the extended winter period and markedly greater prevalence in dark-skinned ethnic subgroups [10,11]. Italian cohorts mirror this pattern, even in regions with substantial solar irradiation: in a representative adult cohort from southern Italy, more than half of participants had 25(OH)D concentrations < 20 ng/mL, while only a minority achieved levels considered adequate (≥30 ng/mL) [11,12]. Seasonal variability, limited time spent outdoors, ageing, and comorbidities are recognized contributors, indicating that low vitamin D status may persist even in ostensibly “sunny” settings [10,11,12]. In line with this concept, recent perspectives emphasize that endogenous synthesis alone may be insufficient to maintain recommended circulating 25(OH)D levels throughout the year, reinforcing the rationale for monitoring and seasonally targeted supplementation strategies [13]. Moreover, maintaining adequate vitamin D status over time has been proposed as a prerequisite for preserving putative protective autocrine/paracrine effects in several tissues, whereas late correction of deficiency might be less effective once disease processes are established [14].

From a nutritional standpoint, fish is often regarded as a key dietary source of vitamin D_3_; however, its actual contribution to population adequacy is constrained by substantial variability in vitamin D content across species, farming practices, and even within the same species. For example, farmed salmon has been reported to contain markedly lower levels of vitamin D than wild salmon, suggesting that food composition tables may be outdated or imprecise [15]. Studies from different markets confirm a wide range of vitamin D_3_ concentrations in both freshwater and marine fish, with some species—including lean fish such as tilapia—showing unexpectedly high values [16,17], as well as the measurable cholecalciferol content documented across commercially consumed fish species [18]. Importantly, even when fish provides meaningful vitamin D_3_ intake, dietary approaches alone are unlikely to eradicate deficiency at scale, given the gap between requirements and realistic consumption patterns [16]. Cooking practices may further influence vitamin D availability, although several domestic methods (including boiling, frying, and grilling) can retain substantial vitamin D content in selected species [17].

Accordingly, strategies to address vitamin D insufficiency include safe sunlight exposure, dietary interventions and food fortification, and supplementation. In routine practice, nutritional-dose vitamin D_3_ supplementation is frequently adopted for individuals with mild insufficiency or to maintain adequate levels, particularly during low-UVB months [11,19]. The EFSA Dietary Reference Values define an Adequate Intake (AI) for adults of 15 μg/day (600 IU/day) under conditions of minimal cutaneous vitamin D synthesis [20,21]. Oral administration is generally preferred in the general population, whereas parenteral routes are reserved for selected clinical settings such as malabsorption or vitamin D resistance [22,23]. Cholecalciferol is typically favored because of its safety profile and minimal monitoring requirements, while calcifediol may be considered in specific conditions, and calcitriol should be restricted to disorders characterized by impaired endogenous activation [22,23]. At nutritional doses, differences in delivery vehicle may be less relevant than the administered dose itself: in healthy adults supplemented with 10 μg/day vitamin D_3_ during late winter, fish oil capsules and solid multivitamin tablets produced similar increases in plasma 25(OH)D over four weeks [7]. This supports the premise that alternative vitamin D_3_ sources may be acceptable if they demonstrate comparable bioavailability and safety.

In parallel with clinical interest, sustainability and circular-economy frameworks are increasingly informing nutraceutical development. Fish and seafood processing generates substantial by-products that may serve as sources of lipid-soluble bioactives, including vitamin D_3_ [24,25]. Beyond extraction, ingredients derived from fish processing by-products are also being explored as functional platforms for vitamin delivery: calcined cuttlefish bone derived from shell by-products has demonstrated high loading efficiency for cholecalciferol and controlled-release kinetics in vitro, supporting the feasibility of side-stream-derived matrices for vitamin D_3_ delivery applications [26]. These approaches may reduce waste streams and reliance on conventional production routes; however, their translational value ultimately depends on demonstrating biological efficacy and safety comparable to established synthetic preparations when administered at commonly used nutritional doses [25]. To date, direct clinical comparisons between fish processing by-product-derived vitamin D_3_ and conventional synthetic vitamin D_3_ remain limited, and dedicated head-to-head trials are only now emerging.

The D-FISH trial was designed to address this gap by testing whether a fish processing by-product-derived vitamin D_3_ supplement is non-inferior to a synthetic vitamin D_3_ supplement in increasing plasma 25(OH)D concentrations over 12 weeks in healthy adults with suboptimal vitamin D status. This non-inferiority framework is particularly suited to sustainability-driven innovation, where demonstrating comparable efficacy and safety to an established standard may be sufficient to support adoption when additional environmental advantages are anticipated. In addition to the primary biochemical endpoint, the protocol includes markers of mineral metabolism and a structured assessment of tolerability and safety, while also exploring early 25(OH)D kinetics through intermediate sampling time points, thereby providing a granular characterization of response dynamics.

## 2. Methods

### 2.1. Study Design

D-FISH is a single-center, randomized, double-blind, parallel-group, non-inferiority trial designed to compare a fish processing by-product-derived vitamin D_3_ nutraceutical with a standard synthetic vitamin D_3_ supplement [27]. Participants will be randomly allocated in a 1:1 ratio to one of the two interventions and will receive study treatment for 12 weeks.

### 2.2. Study Setting

The study will be conducted at the outpatient clinics of the Cardiovascular Medicine Unit, IRCCS AOU di Bologna (Bologna, Italy), which will serve as the single recruiting and follow-up center. Blood samples will be collected on site and subsequently processed and analyzed at the Lipid Laboratory, Department of Medical and Surgical Sciences, Alma Mater Studiorum—University of Bologna.

### 2.3. Eligibility Assessment

Eligibility will be assessed at baseline based on medical history, concomitant therapies, and laboratory values. Full inclusion and exclusion criteria are summarized in Table 1.

Notably, clinically relevant malabsorption syndromes (where oral supplementation may be ineffective and parenteral strategies are often required) would be captured under the general exclusion criterion of any medical or surgical condition that would limit adherence to the study protocol. Participants will be advised to maintain their usual lifestyle habits throughout the study period, including habitual outdoor activities and sun exposure, and to avoid major intentional changes that could substantially modify vitamin D status.

### 2.4. Recruitment and Informed Consent

Potential participants will be identified among adults attending outpatient evaluations (e.g., for dyslipidemia or hypertension) and pre-screened for eligibility. Individuals meeting the inclusion criteria will receive written and verbal information about the study and will have the opportunity to ask questions before deciding whether to participate. Written informed consent will be obtained prior to any trial-specific procedures. Recruitment will span multiple months; the calendar period of enrolment will be recorded, and randomization is expected to distribute seasonal influences across groups. Seasonality-related variability will be considered in sensitivity analyses if imbalances are observed.

### 2.5. Study Products and Administration

Participants will receive one of two oral vitamin D_3_ formulations and will be instructed to take one capsule once daily with the evening meal for 12 weeks. This administration schedule was pre-specified in the approved protocol to standardize intake conditions across participants and to maximize the likelihood of administration in a postprandial setting, thereby limiting variability related to absorption. The intervention uses a nutritional low dose of vitamin D_3_ (600 IU/day), consistent with the EFSA Adequate Intake for adults under conditions of minimal cutaneous synthesis. Both study products are supplied as hard gelatin capsules and will be packaged and labelled in a manner designed to preserve blinding throughout the trial.

#### 2.5.1. Investigational Product: Fish Processing By-Product-Derived Vitamin D_3_

The investigational product contains fish-derived cholecalciferol (vitamin D_3_) obtained from sardine (*Sardina pilchardus*) processing by-products (whole fish), collected by CNR-IRBIM from a professional fishing fleet operating in the Adriatic Sea (Central Mediterranean Sea). Upstream handling follows a predefined cold-chain and timing workflow aimed at preserving the native lipid matrix. Specifically, the raw material is cut and homogenized and subsequently freeze-dried within a maximum of 5 days from catching. During the interval between capture and initiation of freeze-drying, the material is maintained at −20 °C, and after lyophilization, the resulting fish meal is stored at −20 °C until extraction.

The vitamin D_3_-containing fraction is obtained by supercritical CO_2_ extraction (SFE-CO_2_) performed at a supercritical fluids research pilot plant at ENEA. The resulting extract is stored at 4 °C and protected from light prior to formulation. Chemical characterization and standardization are conducted at the University of Camerino using HPLC-DAD on an Agilent 1260 Infinity II system coupled with a diode array detector. Vitamin D_3_ and 7-dehydrocholesterol (7-DHC) are quantified using a previously optimized method. In the extract intended for formulation, vitamin D_3_ and 7-DHC concentrations were 6.18 ± 0.54 μg/g and 789.77 ± 95.02 μg/g, respectively.

To further characterize the lipid matrix accompanying vitamin D_3_, fatty acids are derivatized to fatty acid methyl esters (FAMEs) and analyzed by GC–MS (Agilent 8890 gas chromatograph coupled to an Agilent 5977B mass spectrometer, Agilent Tehcnologies, Santa Clara, CA, USA). Compound identification is supported by the NIST 2020 library, and relative abundances are expressed as percentage peak areas. Overall, polyunsaturated fatty acids (PUFAs) represent the predominant fraction (>43%), followed by saturated fatty acids (~29%) and monounsaturated fatty acids (~19%). Docosahexaenoic acid (DHA) shows the highest relative abundance, and additional ω-3 PUFA species—including eicosapentaenoic acid (EPA) and docosapentaenoic acid (DPA)—are also detected.

For the final dosage form, the extract is microencapsulated at the University of Piemonte Orientale laboratories and formulated into hard gelatin capsules using a defined excipient system including PUFAs, arabic gum, maltodextrin, and pea protein hydrolysate. In support of food safety, contaminant assessment includes trace metals and polycyclic aromatic hydrocarbons (PAHs). In addition, contaminants regulated under EU 2023/915—including dioxins (37 congeners), dioxin-like and non-dioxin-like PCBs (DL-PCB/NDL-PCB), cadmium, mercury, and lead—will be analyzed by a certified laboratory in accordance with applicable legal limits [25].

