#### 2.5.2. Comparator: Synthetic Vitamin D_3_

The comparator contains synthetic cholecalciferol (vitamin D_3_) sourced as a pharmacopoeia-compliant cholecalciferol concentrate powder (Vitamin D_3_ 100; product code 015209; CAS 67-97-0), compliant with the European Pharmacopoeia monograph “Cholecalciferol concentrate powder form”. The declared potency of the raw material is ≥100,000 IU vitamin D_3_/g (≥2500 μg/g), with defined physical specifications including particle size distribution (100% through 30 mesh; ≥90% through 50 mesh; ≤25% through 120 mesh) and loss on drying ≤ 5% (105 °C).

Supplier specifications include predefined limits for heavy metals (total ≤10 ppm; lead ≤ 0.5 ppm; arsenic ≤ 1 ppm; mercury ≤ 0.1 ppm; cadmium ≤ 0.5 ppm) and microbiological acceptability criteria (total aerobic count ≤ 1000 CFU/g; yeasts and molds ≤ 100 CFU/g; *Salmonella* negative/25 g; *Escherichia coli*, *Staphylococcus aureus*, and *Pseudomonas aeruginosa* negative/10 g; Enterobacteriaceae negative/g). The material includes food-/pharmaceutical-grade excipients, and vitamin D_3_ is sourced from wool grease (lanolin).

For the final comparator capsule, vitamin D_3_ is formulated in an oil-based vehicle using medium-chain TG (MCT) as carrier and alpha-tocopherol acetate as antioxidant within a hard gelatin capsule.

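### The stated extract strength, the 600 IU daily dose and the single daily capsule cannot be reconciled from the figures given

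*Protocol article*

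**What the plan says.** All references are to the protocol article.

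- **Dose.** The Abstract says that both arms are treated "at the same nutritional dose (600 IU once daily with the evening meal) for 12 weeks". The Introduction equates 600 IU/day with 15 μg/day, and section 2.5 repeats the 600 IU figure.
- **Units per day.** Section 2.5 says that participants "will be instructed to take one capsule once daily with the evening meal for 12 weeks", and that both products come as hard gelatin capsules.
- **Strength of the fish extract.** In section 2.5.1 the sentence begins "In the extract intended for formulation" and reports that vitamin D3 and "7-DHC concentrations were 6.18 ± 0.54" μg/g for the first and 789.77 ± 95.02 μg/g for the second. The vitamin D3 value is therefore 6.18 ± 0.54 μg/g, and it describes the material that enters the product, not the raw fish or an intermediate.
- **What happens next.** Still in section 2.5.1, the extract is microencapsulated and "formulated into hard gelatin capsules using a defined excipient system including PUFAs, arabic gum, maltodextrin, and pea protein hydrolysate". Standardization is mentioned, but no target content is given, and neither added vitamin D3 nor a concentration step is described.

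**The concern.** The article prints a strength, a dose and a number of capsules for the investigational product. Any two of them constrain the third, and on a simple mass calculation they do not fit together. This differs from a detail that a condensed article leaves out. Either one of the printed figures is wrong, or a step that changes the product's strength is absent from a description that otherwise runs from freeze-drying through extraction to the excipients.

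What is at stake is the interpretation of the primary comparison. Section 2.12 tests the difference in 25(OH)D change, fish-derived minus synthetic, against −5 ng/mL, and the Discussion reads the result as a comparison of sources at an equivalent dose. If the capsules of the two arms did not carry the same amount of vitamin D3, source and dose would be confounded. A failed result could reflect less vitamin D3 rather than poorer bioavailability, and a non-inferior result could not be credited to the source either. Analysis could not repair this after dosing, because capsule content would move together with treatment arm. Separating the two would need an assumed dose-response.

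**Working it through.** **Inputs from the article**

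- Dose: 600 IU = 15 μg (Introduction; section 2.5).
- Extract strength: 6.18 ± 0.54 μg/g (section 2.5.1). The article does not say what the ± denotes; it is treated here as one SD.
- Capsules per day: 1 (section 2.5).

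**Input not in the article**

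- Capsule fill mass. Assumed range: 0.3 to 1.4 g.

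**Step 1. Reproduce the unit conversion.** 600 IU / 15 μg = 40 IU/μg. Section 2.5.2 gives the comparator raw material as 100,000 IU/g, equivalent to 2500 μg/g, so 100,000 / 2500 = 40 IU/μg. The two agree, and the conversion is not the source of the problem.

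**Step 2. Extract needed for one daily dose.** Mass = 15 μg / strength.

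| Strength (μg/g) | Extract for 15 μg (g) |
|---|---|
| 5.64 (−1 SD) | 15 / 5.64 = 2.66 |
| 6.18 (stated) | 15 / 6.18 = 2.43 |
| 6.72 (+1 SD) | 15 / 6.72 = 2.23 |
| 7.26 (+2 SD) | 15 / 7.26 = 2.07 |

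These masses are extract only. Gum arabic, maltodextrin, pea protein hydrolysate and PUFAs come on top.

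**Step 3. Content of one capsule over the assumed fill.** IU = fill (g) × 6.18 μg/g × 40 IU/μg, taking the whole fill as undiluted extract, which is the most favourable case.

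| Assumed fill (g) | IU per capsule | Share of 600 IU |
|---|---|---|
| 0.3 | 74 | 12% |
| 0.5 | 124 | 21% |
| 0.7 | 173 | 29% |
| 1.0 | 247 | 41% |
| 1.4 | 346 | 58% |

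At the top of the range and at +2 SD: 1.4 × 7.26 × 40 = 407 IU, still short of 600 IU.

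**Step 4. How large a change in strength would close the gap.** Required strength = 15 μg / fill.

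- At 1.4 g: 15 / 1.4 = 10.7 μg/g, which is 10.7 / 6.18 = 1.7 times the stated value.
- At 0.3 g: 15 / 0.3 = 50 μg/g, which is 50 / 6.18 = 8.1 times the stated value.

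The 600 IU per capsule is therefore not reproduced at any point of the assumed range.

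**The case against.** The strongest reply is that the contradiction needs a figure the article does not give. No section states a capsule size, fill mass or extract load. That is true, and it is why the point is worded as a failure to reconcile. It does not remove the point: the 2.43 g follows from the article alone, and only the comparison with what a capsule holds is assumed. The conclusion does not change over 0.3 to 1.4 g or with two SDs added to the strength.

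A second reply is that this is a condensed article, that it mentions standardization, and that concentration steps and fill weights may sit in the full protocol or product file. This stands in part. Such a step may exist, but the article ties its strength figure to the material for formulation and then describes only added excipients, so the printed figures still need correcting or completing.

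Some stronger readings are tempting and are not supported:

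- **A reader might infer that the fish-derived capsules are under-dosed.** The article does not show this. A wrong unit or value for the concentration, or an unreported enrichment step, would explain the figures equally well. The high 7-DHC content might also suggest conversion to vitamin D3, but none is described.
- **A reader might fault the comparator because its potency is only a lower limit** ("The declared potency of the raw material is ≥100,000 IU" per gram). That is a raw-material specification. The fill can be set from the actual batch potency, so it contradicts nothing.
- **A reader might call the absence of a finished-capsule assay an error in itself.** An article may leave that to the full document. The assay is requested below only because it settles the discrepancy.
- **A reader might argue that the margin would let an under-filled capsule pass.** A true deficit inside 5 ng/mL is one the design accepts, and any size put on it would need an assumed dose and an assumed response. It is no evidence about capsule content.

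**Conclusion.** The point holds as a discrepancy in the article's own figures. At the stated strength, one daily capsule of 600 IU needs 2.43 g of extract (2.23 to 2.66 g at ±1 SD) before excipients, with no described step that would reduce that mass. Under an assumed fill of 0.3 to 1.4 g of pure extract, a capsule would hold 74 to 346 IU.

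Confidence is high in the arithmetic. It does not extend to any statement about what the capsules actually contain or about which figure is wrong. The capsule capacity and the reading of ± as an SD are assumptions; the first is covered by a range, and the second affects only the spread around 2.43 g.

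Because equal dosing is the premise of the primary comparison and cannot be restored by analysis, the discrepancy should be resolved before the first participant is randomised.

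**What to change.** The sponsor should reconcile the Abstract, the Introduction, section 2.5 and section 2.5.1:

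1. Correct whichever figure is wrong, or describe the step that is missing. Which of these applies is for the sponsor to establish; no dose or number of capsules is proposed here.
2. State the mass of extract per capsule and any concentration or enrichment step between extract and capsule.
3. Before the first randomisation, confirm the vitamin D3 content of the finished capsules in both arms with the HPLC-DAD method already used for the extract.
4. Report the measured content per arm alongside the primary result, so that readers can judge the equal-dose premise directly.

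The cost is one correction to the text and a few runs of an existing assay. First dosing may be briefly delayed if the figures do not reconcile. The sample size and the primary model do not change.
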